#### Baseline measures

In addition to the socio-demographic measures, we include the following measures at baseline to assess the initial level and to account for them as possible moderators or confounders in the effect analyses.

The Prenatal Parental Reflective Functioning Questionnaire (P-PRFQ) [76] is a 14-item measure of *parental reflective functioning* or the pregnant woman’s ability to mentalize. The P-PRFQ is an adaptation of the PRFQ [77] and consists of three subscales: opacity of mental states (4 items), reflecting on the fetus-baby (5 items), and the dynamic nature of mental states (5 items). Cronbach’s alpha is 0.77 for the total score and 0.69–0.77 for the three subscales. Responses are on a Likert scale ranging from 1 to 7 with three different scales: (1) High-Low where 7 = optimal PRF, 1 = low PRF; (2) Low-High where 1 = optimal PRF, 7 = low PRF, and (3) Middle where 4 = optimal PRF, 1 and 7 = low PRF. The total score range is 7–98.

The Hospital Anxiety and Depression Scale (HADS) [78, 79] is a 14-item measure of *anxiety and depression*. HADS consists of the two subscales “anxiety” and “depression,” both ranging from 0 to 21, where low scores indicate less anxiety and depression.

The Experiences in Close Relationship Scale-Short Form (ECR-S) [80] is a 12-item measure of *adult attachment* consisting of the two subscales: “Anxiety” (fear of abandonment and a craving for interpersonal closeness) and “avoidance” (fear of intimacy and interpersonal dependency). Each subscale ranges from 1 to 42, where low scores indicate better attachment.

The Childhood Trauma Questionnaire (CTQ) [81] is a 28-item measure of adverse childhood experiences (ACE). Items are rated on a 5-point Likert scale (Never true, Rarely true, Sometimes true, Often true, Very often true). The CTQ consists of five subscales: emotional abuse, physical abuse, sexual abuse, emotional neglect, physical neglect, and a minimization/denial subscale. Each subscale ranges from 5 to 25, where low scores indicate less trauma experience.

The PTSD-8 inventory [82] is an 8-item measure of *posttraumatic stress disorder (PTSD) symptoms*, including intrusion, avoidance, and hypervigilance. The total score range is 8–32, where a low score indicates a lower level of PTSD.

#### Secondary outcomes

*The parent-child relationship* will be measured by the remaining composites of the CIB: intrusiveness, limit setting, involvement, withdrawal, reciprocity, and negative states.

The short version of the Warwick-Edinburgh Mental Well-being Scale (WEMWBS) [86, 87] is a seven-item measure of *maternal mental health*. A total score is calculated by summing the seven items and converting the raw score according to a published conversion table. Raw score and converted score range from 7 to 35. Higher scores indicate better maternal mental health.

The World Health Organization (WHO)-5 Well-Being Index [88, 89] is a five-item measure of current *mental well-being*. Items that are rated on a six-point Likert scale (all the time, most of the time, slightly more than half the time, slightly less than half the time, some of the time, at no time). The total score ranges from 0 to 100, where a high score indicates better well-being.

The Edinburgh Postnatal Depression Scale (EPDS) [90, 91] is a ten-item measure of mothers’ *depression symptoms*. Depression total score ranges from 0 to 30. A low score indicates fewer depression symptoms, and a score of 11 or above is considered clinically significant.

Being a Mother (BAM-13) [92] is a 13-item measure of a *woman’s satisfaction and experience with being a mother*. Items are rated on a four-point scale (no, hardly ever; no, not very often; yes, some of the time; yes, most of the time). The total score ranges from 0 to 39. A low score indicates higher satisfaction.

The Parental Reflective Functioning Questionnaire (PRFQ) [77] is an 18-item measure of *parental reflective function*. The PRFQ consists of three subscales with score ranges from 6 to 42: (1) Pre-Mentalizing Modes (PRFQ-PM) with six items (a low score indicates better RF); (2) Certainty about Mental States (PRFQ-CMS) with six items (a midrange score indicates better RF); and (3) Interest and curiosity in mental states PRFQ-IC with six items (a high score indicates better RF).

The Parenting Stress Scale (PSS) [93, 94] is an 18-item measure of *parenting stress* that is rated on a five-point scale (strongly disagree, disagree, undecided, agree, strongly agree). The PSS consist of two subscales: Parental Stress (items 3, 4, 9, and 10–16) and Lack of Parental Satisfaction (items 1, 2, 5, 6, 7, 8, 17, and 18). When scoring the subscales LPS items are reversed, and item responses are dichotomized into 0 (strongly disagree and disagree) and 1 (undecided, agree, and strongly agree) and items 2 and 11 are left out. Scores are then summed to subscale scores each ranging from 0 to 9 (PS) and 0 to 7 (LPS), where a low score indicates less stress and higher satisfaction.

The Couple Satisfaction Index [95] is a four-item measure of relationship satisfaction. Items are rated on a 5-point Likert scale (not at all true to completely true). Total scores range from 5 to 20, with higher scores indicating higher relationship satisfaction.

The SEAM Family Profile [96] is a 17-item measure of *family characteristics* such as parental worries and need for additional support. Items are rated on a 3-point scale (most of the time; sometimes; do not know or do not know yet).

The Ages and Stages Questionnaire 3 (ASQ:3) [97] is a 30-item measure of *child developmental progress*. The ASQ:3 consists of the following five subscales: communication, gross motor, fine motor, problem-solving, and personal-social. Cronbach’s alpha ranges from 0.67 to 0.85 for the five subscales for the version for children aged 3 months [98]. The total score range is 0–300 and low scores indicate better development.

The Ages and Stages Questionnaire-Social Emotional 2 (ASQ:SE-2) [99] is a measure of *child social-emotional development*. The ASQ:SE-2 consists of the following seven subscales: self-regulation, compliance, social-communication, adaptive functioning, autonomy, affect, and interaction with people. Total score range is 0–150 (3 months 15 items), 0–260 (12 months 26 items). A low score indicates better development. Cronbach’s alpha ranges from 0.71 to 0.91. Concurrent validity ranges from 71 to 90%. Sensitivity ranges from 78 to 84%, and specificity ranges from 76 to 98% [100].

The Strengths and Difficulties Questionnaire (SDQ) [101, 102] for parents of 2-to-4-year-old children is a 25-item measure of *child behavior and psychopathology*. Items are rated by parents on a 3-point scale (not true, somewhat true, certainly true). The SDQ consists of five domains: hyperactivity/inattention, peer problems, conduct problems, emotional symptoms, and pro-social behaviors. The SDQ also has an additional seven-item impact supplement about daily function.

The 2–5 questionnaire [103] focuses on the development of 2-to-5-year-old children. The full questionnaire consists of 124 items. We include the seven-item language comprehension subscale and the ten-item spoken language subscale. Items are rated on a 3-point scale (does not apply; applies sometimes or to some extent; applies). The total score range for language comprehension is 7–21 and 10–30 for spoken language. A lower score indicates better language skills.

The Mother and Baby Interaction Scale (MABISC) [104] is a ten-item measure of *the mother-infant relationship* that is rated on a 5-point Likert scale (always, most of the time, occasionally, not often, never). The total score range is 0–40, and a high score indicates a better relationship.

The Mother-Infant Relationship Scale (MIRS) [105] is a 19-item measure of *distorted maternal representations*. Distorted maternal representations are disturbed thoughts and feelings that a mother may have about her infant and herself as a parent that influence parenting behaviors and caregiving. Items are rated on a 4-point Likert scale (never to always). The total score range is 15–45, where a low score indicates less distorted representations.

Activities with child consist of 4 items measuring *parent and child interaction* through activities such as singing and reading. The total score range is 4–24. A high score indicates more interaction.

The mothers will also be asked single items about overall health, life satisfaction, breastfeeding intention, breastfeeding duration, use of birth control, supportive network, loneliness, and how they experience the interdisciplinary collaboration between all clinicians involved (e.g., midwife, general practitioner, health visitor, family therapist). If the mother is not employed, she will be asked questions about indicators for progression toward employment (belief in own skills, mastery of health, and work identity). These items were developed in the employment indicator project [106].

#### Administrative data

When all children have turned 2 years old, we will retrieve data on all families from Danish administrative data such as the Population Statistics Register, the National Patient Register, the National Prescription Register, the National Health Insurance Service Registry, Oral Health Register, the Education Register, and the Danish Rational Economic Agents Model (DREAM). With these data, we can examine outcomes such as vaccinations, child examinations at the general practitioner and dentist, use of social and health care services including emergency visits, use of medication, and information about housing, education, and labor market participation for the parents.

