### Eligibility criteria {10}

#### Inclusion and exclusion criteria

Pregnant women at least 15 years old who are characterized as antenatal care groups 3 or 4 according to the Danish Health Authority’s recommendations for antenatal care [69] are invited to participate in the study. Pregnant women I care groups 3 and 4 have complex physical, mental, or social problems, or harmful substance abuse and need intensive care from an interdisciplinary team as they have a higher risk of preterm birth or pregnancy complications [70–72]. The pregnant women in the study may experience one or more the following characteristics: the authorities worry about the well-being of the child, the family has no support network, there is a history of childhood trauma or neglect, parental depression or anxiety, social problems, economic problems, unstable family relationships, and alcohol or substance abuse. Participation in the MTB intervention is voluntary.

Women are excluded if they fulfill one or more of the following criteria: (1) a child older than 3 years old living full-time with the family, (2) current severe substance abuse, (3) severe psychotic illness (F20), (4) profound or severe learning disabilities, (5) life-threatening illness in parent or child, and (6) not able to fill out questionnaires in Danish.

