### Outcomes {12}

Data are collected at five time points: T0: baseline immediately after recruitment, T1: baseline part two before the child is born, T2: when the infant is 3 months old, T3: when the infant is 12 months old, and T4: when the infant is 24 months old.

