### Recruitment {15}

Participants will be recruited by municipal frontline workers by phone or in person. The municipalities get information about pregnant women in care groups 3 and 4 from the maternity wards, from municipal interdisciplinary meetings about pregnant women at higher risk of adversity, or from child protective services if they receive a reporting about the family or if the pregnant woman previously has been supported by child protective services. Families in the target group who are eligible for the MTB intervention will be invited to participate in the study and will be offered either MTB or the control condition. The frontline worker will give oral information about the study and give the study leaflet to the family. If the pregnant woman gives consent to participate, her partner is also be invited to participate. The consent form and other related documentation given to participants are available from the authors on request.

After receiving consent, the frontline worker will register the pregnant woman (and partner) through a registration form in SurveyXact. Research staff at VIVE then send the baseline questionnaire to the participant (and partner) by text message and by email. Clinicians ask the participant (and partner) to fill out the second part of the baseline questionnaire (childhood trauma experiences and PTSD symptoms) at a home visit and will conduct the Pregnancy Interview with the intervention mothers and partners. Frontline staff will inform VIVE when the child is born.

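### Covariate adjustment carries the comparison, yet beyond municipality it relies on a p < 0.1 screen with self-reports as the named confounders; no fixed pre-enrolment covariates (care group, register history) are specified

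*Protocol article*

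**What the plan says.** **Allocation.** Implementation {16c} makes a woman's condition depend on the training wave of her site. After training, sites still recruit CAU women when the MTB team has no room or the birth is near. The four municipalities added later were not randomised, and one of them contributes MTB families only.

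**Primary outcome.** Table 2 and section {18a} schedule the CIB video at 12 and 24 months only.

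**Adjustment.** Statistical methods {20a} adjusts for municipality and the outcome's baseline value, and adds variables that differ between arms at p < 0.1. Baseline measures gives one purpose of its questionnaires as "to account for them as possible moderators or confounders in the effect analyses".

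**Order of events.** Under Recruitment {15}, eligible families "will be invited to participate in the study and will be offered either MTB or the control condition". Consent and registration come next, and then: "Research staff at VIVE then send the baseline questionnaire to the participant (and partner) by text message and by email". Outcomes {12} agrees: "T0: baseline immediately after recruitment". For trauma and PTSD symptoms, "Clinicians ask the participant (and partner) to fill out the second part of the baseline questionnaire" at a home visit. The same clinicians conduct the Pregnancy Interview with intervention mothers. Section {17a} says participants cannot be blinded.

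**Other data.** Eligible women are those "characterized as antenatal care groups 3 or 4". Administrative data plans register retrieval for all families once every child has turned 2, and continues: "With these data, we can examine outcomes such as vaccinations". Section {20c} imputes from the available baseline data without naming a source.

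**The concern.** With no individual randomisation and no baseline CIB score, the primary contrast is only as good as its covariates. The stated rule has two weaknesses. First, a p < 0.1 screen selects on the size of the observed imbalance and ignores how prognostic the variable is, so a moderate imbalance on a strong predictor can be left out. Second, the variables named as confounders are answered after a condition has been offered in an unblinded trial, and they are open to non-response.

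Antenatal care group and pre-enrolment register history do not share the second weakness. Knowledge of the arm cannot alter a record dated before enrolment, and such a record can exist for a woman who skips a questionnaire. The protocol gives neither a role in adjustment. At stake is residual confounding of the primary effect, and a weaker imputation model than the trial could have.

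**Working it through.** **1. The plan's own figure, used here only as a yardstick.** Sample size {14} gives SMD 0.44, two-sided alpha 0.05, 80% power and a 1:2 ratio. Controls = (1.960 + 0.842)² × (1 + 1/2) / 0.44² = 60.8, so 61 controls and 122 intervention, 183 in total. This reproduces, and nothing below changes it.

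**2. Candidate covariates side by side.**

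| Source | Fixed before the offer? | Coverage | Covariate use named |
|---|---|---|---|
| Municipality | Yes | All women | Yes, always |
| T0 questionnaires | No | Open to non-response | If p < 0.1 |
| T1 trauma and PTSD | No, home visit | Open to non-response | If p < 0.1 |
| Antenatal care group | Yes, it defines eligibility | Needed for every woman; storage of the 3-versus-4 value not stated | None |
| Register history before enrolment | Yes | Retrieval planned for all families | None |

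The baseline-outcome term in {20a} has nothing to act on for the CIB. The primary model is therefore municipality plus whatever passes the screen.

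**3. Bias from a missed confounder (illustration).** The imbalance d and the correlation r with sensitivity are assumptions, not figures from the protocol. Bias = r × d.
- d = 0.2, r = 0.3: 0.06 SD; 0.06 / 0.44 = 14%.
- d = 0.3, r = 0.3: 0.09 SD; 0.09 / 0.44 = 20%.

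These are biases with the factor wholly uncaptured. Municipality or a correlated questionnaire score would remove some of it.

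**4. How often the screen admits such a factor (illustration).** Take the planned 75 and 175 women, no clustering, and a covariate in SD units. SE = √(1/75 + 1/175) = 0.138. The probability of passing is Φ(d/SE − 1.645) + Φ(−d/SE − 1.645).
- Observed d = 0.3: 0.70.
- Observed d = 0.2: 0.42.
- Observed d = 0.1: 0.19.

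Suppose knowledge of the arm shifted answers by 0.1 SD against the true imbalance. A true 0.3 would then look like 0.2 (pass 0.42), and a true 0.2 like 0.1 (pass 0.19). If the shifted variable were adjusted for anyway, 0.3 × 0.1 = 0.03 SD of bias would remain. The protocol gives no evidence that such a shift occurs.

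**5. What cannot be computed.** The bias remaining after the planned covariates, and the precision gained over them, need the joint distribution of questionnaire and register variables. The protocol does not give it.

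**The case against.** The strongest reply is that this is an enhancement and not an error. The register sentence is permissive, the covariate rule in {20a} and the imputation rule in {20c} name no data source, and a fuller covariate list may sit in a document not shown. This stands against one tempting inference: a reader might conclude that registers are reserved for outcomes and that the data go unused. The protocol does not say so; it only names no covariate use. It does not rescue the screen, which {20a} states and which a fixed set would improve.

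A reader might also infer that adjustment rests on questionnaires alone, or that registers would supply complete confounder data. Neither is supported. Municipality is always adjusted for. The listed registers do not measure reflective functioning or attachment style, so they can supplement the questionnaires but not replace them.

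Other parts of the reply also hold:
- T0 already records education and occupation, and HADS covers anxiety and depression. Reported age or education is unlikely to depend on the arm.
- The exclusions for current severe substance abuse and severe psychotic illness narrow the range of the related register variables.
- That a woman knows her condition at T0 follows from the order of events and is not stated outright. At T1 it is clearer.
- The figures in step 3 compare with no capture of the factor, so they must not be read as the bias of the planned analysis.
- The Discussion reports baseline measures from 254 women against a target of 250, so a new field on the registration form would come too late for nearly all of them.

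**Conclusion.** The point holds as a cheap improvement to a stated rule. The allocation is open to confounding, the primary outcome has no baseline value, and beyond municipality the plan uses a p < 0.1 screen with post-offer self-reports as its named confounders. A short fixed set of pre-enrolment covariates, which knowledge of the arm cannot change, is better than that rule.

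The size is illustrative only: 0.06 to 0.09 SD if an imbalance of 0.2 to 0.3 SD on a factor correlating 0.3 with sensitivity escapes the planned adjustment. Imbalance and correlation are both assumed. Neither the residual bias beyond the planned covariates nor the gain in precision can be stated from the protocol. Register records are free of arm influence only if restricted to dates before enrolment; later records may be affected by treatment and should not be adjusted for.

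**What to change.** In Statistical methods {20a}, pre-specify a short set entered whatever its baseline p-value, alongside municipality and the questionnaire covariates:
- antenatal care group (3 versus 4), obtained retrospectively from municipal or maternity records;
- from the planned registers, restricted to dates before enrolment: psychiatric or substance-related hospital contact, psychotropic prescription, education, and labour-market attachment.

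Use the set in the 24-month model and in the multiple imputation. At 12 months, use it in the main model or, if results are reported before the extract arrives, in a pre-specified sensitivity model.

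The cost is about five degrees of freedom (one per item if each is binary), a longer look-back in an extract already planned for about the end of 24-month follow-up, retrospective collection of care group, and a possible delay to the 12-month analysis.

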#### Fidelity

In addition to the elements of interventionist training and ongoing supervision for fidelity monitoring, implementation process variables will be collected from each site. For intervention families, the MTB clinician must register each visit with the family. For all families, we will collect data from the municipality on what they have been offered (apart from MTB). We ask for information about who is providing the support and the intensity of the support (number and length of sessions). We also ask if the child has been placed in out-of-home care.

### Participant timeline {13}

The protocol conforms to the Standard Protocol Items: Recommendations for Interventional Trials (SPIRIT) guidelines (Fig. 2).

**Fig. 2 Fig2:**
[figure not shown]
Schedule of enrolment, allocation, intervention, and assessments

### Sample size {14}

Power analysis was carried out in the design phase to assess the statistical power for testing the main hypothesis. The power calculation is based on a meta-analysis of interventions aimed at improving parenting sensitivity [57]. The overall average effect size was 0.44 (standardized mean difference, SMD). We expect controls to constitute about one-third of the sample. For normally distributed outcomes and using a two-sided alpha of 0.05, and a beta of 80%, we would need a total of 183 participants (61 control and 122 intervention) for an effect size of 0.44 SMD. To leave room for dropout, we plan to recruit 250 participants (75 control and 175 intervention).

### Recruitment {15}

Participants will be recruited by municipal frontline workers by phone or in person. The municipalities get information about pregnant women in care groups 3 and 4 from the maternity wards, from municipal interdisciplinary meetings about pregnant women at higher risk of adversity, or from child protective services if they receive a reporting about the family or if the pregnant woman previously has been supported by child protective services. Families in the target group who are eligible for the MTB intervention will be invited to participate in the study and will be offered either MTB or the control condition. The frontline worker will give oral information about the study and give the study leaflet to the family. If the pregnant woman gives consent to participate, her partner is also be invited to participate. The consent form and other related documentation given to participants are available from the authors on request.

After receiving consent, the frontline worker will register the pregnant woman (and partner) through a registration form in SurveyXact. Research staff at VIVE then send the baseline questionnaire to the participant (and partner) by text message and by email. Clinicians ask the participant (and partner) to fill out the second part of the baseline questionnaire (childhood trauma experiences and PTSD symptoms) at a home visit and will conduct the Pregnancy Interview with the intervention mothers and partners. Frontline staff will inform VIVE when the child is born.

